## Abstract

**Background:**

Potentially inappropriate prescribing in older people is common in primary care and can result in increased morbidity, adverse drug events, hospitalizations and mortality. In Ireland, 36% of those aged 70 years or over received at least one potentially inappropriate medication, with an associated expenditure of over €45 million.

The main objective of this study is to determine the effectiveness and acceptability of a complex, multifaceted intervention in reducing the level of potentially inappropriate prescribing in primary care.

**Methods/design:**

This study is a pragmatic cluster randomized controlled trial, conducted in primary care (OPTI-SCRIPT trial), involving 22 practices (clusters) and 220 patients. Practices will be allocated to intervention or control arms using minimization, with intervention participants receiving a complex multifaceted intervention incorporating academic detailing, medicines review with web-based pharmaceutical treatment algorithms that provide recommended alternative treatment options, and tailored patient information leaflets. Control practices will deliver usual care and receive simple patient-level feedback on potentially inappropriate prescribing. Routinely collected national prescribing data will also be analyzed for nonparticipating practices, acting as a contemporary national control. The primary outcomes are the proportion of participant patients with potentially inappropriate prescribing and the mean number of potentially inappropriate prescriptions per patient. In addition, economic and qualitative evaluations will be conducted.

**Discussion:**

This study will establish the effectiveness of a multifaceted intervention in reducing potentially inappropriate prescribing in older people in Irish primary care that is generalizable to countries with similar prescribing challenges.

**Trial registration:**

Current controlled trials ISRCTN41694007

## Background

### Prescribing in older people

Older people are among the biggest consumers of healthcare services, particularly drug therapy [1]. They tend to have multiple conditions, requiring multiple drug treatments [2]. They also experience age-related changes in physiology and body composition that influence the body’s ability to process medications efficiently, in terms of both pharmacokinetics (the body’s ability to absorb, distribute, metabolize and excrete a drug) and pharmacodynamics (the drug’s physiological effects) [3,4]. Thus, prescribing for older people is a complex and challenging task, with the potential for adverse outcomes including drug-drug interactions, adverse drug reactions and potentially inappropriate prescribing (PIP) [5].

The term ‘potentially inappropriate prescribing’ covers a number of suboptimal prescribing practices, particularly the use of medicines that introduce a greater risk of adverse drug-related events where a safer and equally effective alternative is available to treat the same condition [6]. Inappropriate prescribing in older people can result in increased morbidity, adverse drug events, hospitalizations and mortality [7-9]. Potentially inappropriate prescribing may be measured with explicit (criterion-based) or implicit (judgment-based) tools [9]. A recently developed explicit process measure, the Screening Tool of Older People’s Prescriptions (STOPP), has been published for use in European settings [10].

When these criteria were applied to an Irish pharmacy claims database (containing the prescription records of 97% of those aged ≥70 nationally), it was found that 36% of those aged ≥70 years received at least one potentially inappropriate medication. Total PIP expenditure was estimated at over €45 million (or 9% of expenditure on pharmaceuticals in that age group) [11]. The clinical and economic burden of PIP is an important public health concern and it is important to minimize PIP where possible, to increase patient safety and encourage cost-effective prescribing.

### Interventions to change prescribing

Changing professional practice is a complex and difficult task. While the usefulness of behaviour change theory in intervention and implementation research has been questioned, [12,13] there is general consensus that interventions are more likely to have an impact when they target all stages of behaviour change [14]. Studies to date have yielded mixed results in terms of which intervention types are most effective in improving prescribing and there is no one interventional strategy that has proved to be most effective [15]. Strategies shown to be effective for improving prescribing outcomes include educational outreach visits (academic detailing) [16] and interventions involving a pharmacist [17]. Pharmacist services, such as conducting medicines reviews or providing advice to general practitioners (GPs) may lead to improvements in prescribing outcomes, including more appropriate prescribing in older people [9,17-21]. Patient-mediated interventions do not consistently show effects in improving prescribing [22]; however, evidence suggests that providing patients with information is important. Patient information leaflets may be helpful in improving patient outcomes, and older people appreciate receiving brief, clearly written information leaflets [23,24]. A number of commentators have argued that a multifaceted intervention, an approach that combines a number of techniques within a single intervention [20], may be more likely to work than any one single intervention [9,25,26].

### Study aim and objectives

The aim of this study is to determine the effectiveness and acceptability of a complex, multifaceted intervention in reducing the level of PIP in primary care. The intervention combines academic detailing, medicines review with web-based pharmaceutical treatment algorithms that provide recommended alternative treatment options, and tailored patient information leaflets. The intervention development was informed by the Medical Research Council (MRC) guidelines for the development and evaluation of randomized controlled trials (RCTs) [27,28]. It was piloted with a group of five GPs and found to be feasible and acceptable within this group.

Secondary objectives are to evaluate the effect of the intervention on patient outcomes in terms of the number of GP visits, the number of hospitalizations, patient well-being, beliefs about medicines and health status. The views and experiences of participants concerning the possible reasons for the intervention to be effective or ineffective will be explored using qualitative methodology. In addition, an economic evaluation will be carried out.

## Methods/design

### Trial design

The OPTI-SCRIPT study is a pragmatic two-arm cluster RCT, incorporating qualitative analysis. Qualitative approaches can contribute in several ways to the development and evaluation of health interventions; they have been used during intervention development and piloting and will be used to undertake a process evaluation of the trial [29]. The study design was developed in line with the Consolidated Standards of Reporting Trials (CONSORT) statement extension to cluster RCTs [30]. A cluster design was chosen to avoid the possibility of contamination across arms. A GP who is treating both intervention and control patients might find it difficult to behave differently towards each group [31]. The trial will be conducted in primary care with GP practices as the unit of randomization. A practice can be a single-handed GP or can comprise two or more GPs (group practices); however, not all GPs in group practices may wish to participate. Participation may be decided by one GP on behalf of the group practice, in which case that GP will be the main point of contact for the study. We will keep a record of participating GPs. Participation in the intervention arm will be defined as attendance at the academic detailing visit and undertaking medicines reviews, while participation in the control group as providing patient prescription data. Practices that do not meet these criteria will be considered lost to follow-up (see Figure 1). The intervention will be delivered at the GP level while the unit of analysis will be at the individual patient level, in terms of medicines prescribed, adjusting for clustering.

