### Data collection

Prescription data, process-of-care measures and patient-reported outcomes will be collected at baseline and on intervention completion, that is, the point at which all ten reviews have been completed (this must be within a 6 to 8 week period). Follow-up data will also be collected 12 months after the intervention completion. Data will be collected from the following sources:

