#### GP medical chart

Patient records will be used to collect the drug-specific outcome data for all participants at baseline and follow-up. Process-of-care data, such as health-service utilization (for example, the number of GP visits) will also be collected for intervention and control patients.

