### Plan of analysis

The minimization process will ensure balance between treatment groups in terms of certain prognostic factors. Descriptive statistics will be used to evaluate differences in other baseline characteristics between participating physicians and patients in the two arms of the trial. The primary analysis will be carried out using multilevel modeling (such as mixed linear effects modeling or generalized estimating equations [41]) to control for the effects of clustering and baseline differences. All analysis will be conducted under the intention-to-treat principle.

Subgroup analyses will be performed for the primary outcome to assess whether the intervention varies by practice size or GP characteristics, such as sex or number of PIP drugs. As this is a pragmatic trial, a secondary, per-protocol analysis will also be conducted. This form of analysis includes only those participants who completed the treatment protocol originally allocated, providing results on the efficacy of the trial [42].

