### Data management and protection

A trial steering committee will be established. The aim of the trial is to identify older patients with existing PIP. These patients will be known to the research team by study ID number only. One member of the research team (BC) will have access to patient contact details for follow-up data collection purposes. The GP remains responsible for all treatment decisions made. Informed consent will be sought from all study participants. All data collected will be stored on a secure, password-protected server. All interviews will be audio recorded and transcribed, the digital recording overwritten and the transcripts pseudo-anonymized and stored on a secure, password-protected server.

The academic detailing will demonstrate the process of the medicines review with the intervention practices but the research team will not monitor how the GP implements the study protocol after this, other than to remind the practices to complete the process within the allotted period. This study is pragmatic in nature, measuring the intervention’s effectiveness in real clinical practice.

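### Loss to follow-up depends on delivering the intervention in one arm and on supplying data in the other, which conflicts with the intention-to-treat analysis

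*Protocol article*

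**What the plan says.** All references are to the protocol article.

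- **Trial design**, intervention arm: "Participation in the intervention arm will be defined as attendance at the academic detailing visit and undertaking medicines reviews".
- **Trial design**, control arm, in the same sentence: "while participation in the control group as providing patient prescription data".
- **Trial design**, consequence for both arms, with a pointer to the flow chart in Figure 1: "Practices that do not meet these criteria will be considered lost to follow-up".
- **Plan of analysis**: "All analysis will be conducted under the intention-to-treat principle". A per-protocol analysis is planned separately, as a secondary one: "This form of analysis includes only those participants who completed the treatment protocol originally allocated".
- **GP medical chart**, source of the prescribing outcomes: "Patient records will be used to collect the drug-specific outcome data for all participants at baseline and follow-up".
- **Data collection**, first post-baseline collection: "on intervention completion, that is, the point at which all ten reviews have been completed". The later collection is 12 months after intervention completion.
- **Data management and protection**, aim: "This study is pragmatic in nature, measuring the intervention’s effectiveness in real clinical practice".

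**The concern.** The control criterion is ordinary availability of outcome data. The intervention criterion is adherence to the allocated treatment. One term, lost to follow-up, therefore carries two meanings, and only the intervention arm can lose a practice whose outcome could still be measured.

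Intervention practices that never engage are plausibly the ones whose prescribing changes least. Removing them from one arm after randomization would tend to favour the intervention on both primary outcomes. It would also leave the primary comparison close to the per-protocol analysis that the plan labels secondary. In a trial meant to measure effectiveness in routine practice, failure to deliver is part of the effect being estimated.

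Two features add to this. The criterion gives no minimum number of reviews, so a practice that completes some of its ten could be classed either way after allocation, in a trial where GPs are not blinded. And if a practice is treated as lost while the trial is running, its follow-up data may never be requested. A later analysis plan cannot recover data that were not collected.

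**Working it through.** **Step 1. Apply the Trial design wording to each kind of practice.**

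| Arm | Intervention delivered | Follow-up prescription data obtainable | Status under the wording |
|---|---|---|---|
| Intervention | yes | yes | participating |
| Intervention | no | yes | lost to follow-up |
| Control | not applicable | yes | participating |
| Control | not applicable | no | lost to follow-up |

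The second and third rows are the problem: the same data are available, but the status differs. The fourth row shows that control practices can be lost too, but only because data are missing.

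**Step 2. Look for a rule elsewhere that keeps the second-row practice in.**

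- Plan of analysis invokes intention-to-treat but does not mention practices classed as lost.
- The chart-data section covers all participants and does not make extraction depend on a review. Under Recruitment and allocation, baseline data are collected before allocation. The outcome is therefore obtainable in principle.
- Data collection ties the first follow-up to completion of all ten reviews, and the 12-month follow-up counts from there. A practice that does no reviews never reaches the first time point, and the article gives no other one for it.
- Both sample size calculations use the same term, loss to follow-up, for a 10% inflation, which is its usual sense of missing outcomes.

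No section says that such a practice is still followed and analysed as randomized.

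**Step 3. The plan's own figure, to place the loss allowance.** Inputs from Sample size: 100% versus 90%, 80% power, 5% one-sided, ICC 0.025, ten patients per practice, 10% loss.

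- The two-proportion formula with continuity correction gives 77 per arm, 154 in total.
- Design effect: 1 + (10 − 1) × 0.025 = 1.225, and 154 × 1.225 = 188.7.
- Loss allowance: 188.7 / 0.90 = 209.6, close to the stated 212 patients and 22 practices.

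The stated size is reproduced to within about 1% and is not in dispute. The 10% is applied to the total. One practice of ten patients is 10/220 = 4.5% of the target, and the target of 220 is already above 212.

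**Step 4. Size of the possible bias.** The article gives no non-delivery rate, so these are assumptions: 11 practices of equal size per arm; a 10-point reduction where reviews are delivered (the plan's target difference); no reduction where they are not; *k* intervention practices do not deliver.

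- Estimate if the *k* practices are dropped: 10 points.
- Intention-to-treat effect: 10 × (11 − *k*)/11.
- Overstatement factor: 11/(11 − *k*).

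| *k* | Estimate with practices dropped | Intention-to-treat effect | Factor |
|---|---|---|---|
| 1 | 10.0 | 9.1 | 1.10 |
| 2 | 10.0 | 8.2 | 1.22 |
| 3 | 10.0 | 7.3 | 1.38 |

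The same factors apply to the second primary outcome. A 30% relative reduction in delivering practices becomes 30 × (11 − *k*)/11 = 27.3%, 24.5% or 21.8% by intention to treat.

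**The case against.** The best defence is that the sentence is only a label for the flow chart. It points to Figure 1, which is not shown in the text at hand. It does not say that data collection stops or that the practices leave the analysis. The explicit analysis statement is intention-to-treat, outcome data are to be collected for all participants, and a separate per-protocol analysis would have little purpose if non-delivering practices were already out of the primary set. Analysis sets are also commonly left to the analysis plan.

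This reading is possible, and it limits the point. A reader might infer that the protocol prescribes a per-protocol exclusion in one arm; the article does not state that. What remains is that the wording, followed literally, produces the conflict, that no section resolves it, and that the definition governs trial conduct as well as analysis.

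Three further inferences go too far:

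- *Control practices can never be lost.* They can, if they supply no prescription data.
- *One lost practice nearly exhausts the loss allowance.* One practice is 9.1% of an arm of 11, but the allowance is on the total, where it is 4.5%.
- *The percentages measure the bias in this trial.* They rest on complete non-delivery, exactly zero effect without reviews, and exclusion. The Intervention section provides for a reminder and a negotiable extension, and no minimum number of reviews is set, so complete non-delivery may be uncommon.

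It is also fair to say that practice staff supply the prescription records at recruitment. If follow-up works the same way, a disengaged practice may genuinely yield no data. That would be true loss, and an identical definition in both arms would classify it correctly.

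**Conclusion.** The point holds as a conflict between the participation definition under Trial design and the intention-to-treat statement under Plan of analysis. The definition makes loss to follow-up depend on treatment delivery in one arm only. Whether non-delivering practices would actually leave the primary analysis is not stated either way.

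If they did, the likely direction is overstatement of benefit on both primary outcomes: by a factor of 1.10 to 1.38 for one to three such practices, under the assumptions in the working. The direction is probable rather than certain, because it depends on non-delivering practices changing less than the others. If they are followed and analysed as allocated, there is no bias and only the wording needs correcting. The sample size is unaffected.

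**What to change.** 1. In Trial design and the flow chart, define loss to follow-up identically in both arms: no follow-up prescription data obtainable.
2. Seek follow-up prescription data from every randomized practice, whether or not the detailing visit or the reviews took place.
3. Give the follow-up a time point that does not depend on completing the reviews, and reconcile Data collection with it. Table 3 already names 4 and 12 months for GP visits and hospital admissions, so fixed times are not new to the plan.
4. State under Plan of analysis that these practices and their patients stay in the allocated arm for both primary outcomes.
5. Report the detailing visit and reviews as adherence, and use them only to define the per-protocol set already planned as secondary.

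The cost is a few sentences, some extra data extraction from practices that did not deliver, and possibly a smaller estimated effect. Trial status reports that patient identification was only just starting, so at that stage the change could be made before any follow-up data were due.

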**Figure 1 F1:**
[figure not shown]
Flow of practices and patients through RCT.

### Study population

Practices are eligible to participate if they have approximately 80 or more older patients (aged ≥70 years) on their patient panel (based on the need to recruit 10 patients per practice, and allowing for refusals) and they are based in the greater Dublin area (to facilitate the academic detailing process).

Practices are excluded where they have been involved in the development and piloting of the intervention or other concurrent medication quality related studies.

Patients will be considered eligible if they are aged 70 years or over and they are being prescribed one or more selected potentially inappropriate prescriptions on a repeat basis (only patients with an existing PIP will be included, as the intervention is specifically targeting the management of PIP).

Patients will be excluded if they have significant mental or physical illness that is likely to impair their ability to participate in the study, or they are unable to attend the GP surgery for consultation (for example, they are nursing home residents) or they are participating in another medication quality related study.

### Recruitment and allocation

Potentially eligible practices (based in the greater Dublin area) will be identified from the Health Research Board (HRB) Primary Care Research Centre research network. All eligible practices will be invited to participate by an email (or letter where email address is unavailable), which will include a study information leaflet outlining steps of the intervention and availability of continuing medical education (CME) points for participation. When a practice agrees to participate, a member of staff (for example, a GP, practice manager or nurse) will be selected by the practice. The research team will instruct the designated person on how to identify a random sample of 50 patients aged 70 years and over from the patients of participating GPs within the practice. They will pseudo-anonymize the records by assigning the patients a study ID and send a copy of the pseudo-anonymized prescription records to the research team, where a research pharmacist will generate a list of potentially eligible patients, that is, patients with PIP. A maximum of ten patients per practice is required; if more than ten patients are identified, ten patients will be selected at random from the list of eligible patients. Eligible patients will be sent a letter of invitation, a patient information leaflet and a consent form, asking them to participate and answer a questionnaire. Prior to practice allocation, baseline patient data (including prescription data, process-of-care measures and patient-reported outcomes – see sections on outcomes and data collection) will be collected. Practices will then be assigned to intervention or control using minimization. This approach offers the advantage of ensuring balance between the groups [32] in terms of prognostic factors: in this case, practice size (number of whole-time-equivalent GPs) and practice location (urban or rural, where an urban area is defined as a relatively small centre of population, with 5000 or more residents [33]). A chart of the flow of participants through the study is presented in Figure 1. Because of the nature of the intervention, it is not possible to blind GPs or participants to the intervention.

